## Data collection and management

### Plans for assessment and collection of outcomes {18a}

Data will be collected from multiple sources: pre- and post-survey responses as well as the final essay via the Qualtrics platform, interaction logs with ChatGPT for the intervention group, writing data in the text editor for the control group, gaze and pupil-related data from the eye tracker, and hemodynamic activity data from the fNIRS. In particular, the surveys will capture participants’ background characteristics that may contribute to heterogeneity effects (Table 2). The pre-survey will include measures such as participants’ initial interest in analytical writing and their motivation to achieve a high score on the writing task. The post-survey will include participants’ frequency of ChatGPT use, English ability, their native language, writing ability, critical thinking ability, and demographic details, including their age, gender, race, academic year, and academic major. Background characteristics are mainly collected in the post-survey, unless necessary to be in the pre-survey, to avoid potential signaling effects that could influence participants’ writing behavior during the writing task. The data retrieved from all sources will be anonymous. Data downloaded will be stored on an encrypted and secure server. The data will be deleted 5 years after the study has been completed.

**Table 2 Tab2:** Background information in the pre- and post-surveys

Survey	Construct	Items and response
Pre-survey	Initial interest in analytical writing	On a scale of 1 to 7, how much do you agree or disagree with the following statements? (1 being “strongly disagree” and 7 being “strongly agree”) 1. I find analytical writing enjoyable 2. I enjoy writing an analytical essay 3. I like learning new skills about analytical writing
	Motivation to achieve a high score in the writing task	On a scale of 1 to 5, how motivated are you to achieve a high score in your essay? (1 being “not at all motivated” and 5 being “extremely motivated”)
Post-survey	Frequency of ChatGPT use	In the past month, how often have you used ChatGPT for writing tasks? Consider all forms of writing tasks, including but not limited to analytical essays, academic papers, reports, reading reflections, and discussion posts. Note that there are no requirements on how you used ChatGPT for these tasks • Never (not used it or not heard of it) • Occasionally (1–3 times a week) • Everyday or almost everyday (> 3 times a week)
	English ability	What is your level of English proficiency? • My English level is basic (I can describe simple terms related to areas of immediate need) • My English level is intermediate (I can produce clear, detailed text on a wide range of subjects) • My English level is proficient (I can produce text spontaneously and precisely) • I am a native speaker of English
	Native language	What is your native language? (This question will be skipped if the participant answered “I am a native speaker of English” in the English ability question.)
	Writing ability	In the past month, how often have you written essays? • I rarely write essays • I write occasionally for academic purposes (e.g., class assignments) • I regularly write for academic or work-related tasks (e.g., reports, academic papers) • I write daily as a significant part of my job or academic work
	Critical thinking ability	How much are you trained in critical thinking? • I have never received any formal training in critical thinking • I have taken workshops or courses that emphasizes critical thinking • I have a degree in a field that emphasizes critical thinking • I have extensive formal or professional experience in critical thinking
	Age	What is your age?
	Gender	What is your gender? • Man • Woman • Non-binary • Prefer not to say
	Race/ethnicity	What is your race or ethnicity (select all that apply)? • Asian • Black/African • Hispanic/Latino • White/Caucasian • Other, please specify:
	Academic year	What academic year are you in? • Undergraduate, first-year of bachelor’s degree • Undergraduate, second-year of bachelor’s degree • Undergraduate, third-year of bachelor’s degree • Undergraduate, fourth-year of bachelor’s degree • Undergraduate, fifth-year or above of bachelor’s degree • Graduate, master’s degree • Graduate, doctoral degree • Law degree • Medical degree • Other, please specify: • Not applicable
	Academic major	What is your major? • My major is: • I’m undecided

### Plans to promote participant retention and complete follow-up {18b}

For each participant, the study will take approximately 1.5 h. The participant may withdraw from the study at any time. Their compensation will be rounded based on the amount of time they spend in the experiment. There is no follow-up study.

### Data management {19}

All data collection during the experiment will be anonymous. The experimental data collection process will be separated from the collection process for the personally identifiable data required for scheduling and consent purposes. Pseudonymized IDs will be used to join all data sources. Survey data will be collected on the Qualtrics platform. Except for Qualtrics, third parties will not have access to this data. Interaction log with ChatGPT will be collected on the ChatGPT platform under the study team’s account, exported, and removed from the platform after each participant completes their session. All other data (e.g., eye-tracking data, fNIRS data, writing data in the text editor) will be locally collected on the computers in the experiment room. All data will be uploaded to the university-owned, encrypted cloud storage service. Only the study team will have access to the data.

### Confidentiality {27}

Data collected on the survey, ChatGPT, and the local computer will be joined using pseudonymized IDs for data analysis. Participants’ personal information (i.e., name, contact information, and experiment time slot) will be collected separately only for contacting and scheduling purposes, and in case the participant would like to withdraw their data from the study. The principal investigator and research staff who conduct the experiment will have access to this information and have been trained before the study to ensure that they understand the rules for confidentiality and data protection. No other researchers on the team will have access to the data on personal information. No data will be captured on paper/physical media other than the signed consent form and the compensation confirmation form. The two forms will be stored in a locked cabin in the experiment room.

### Plans for collection, laboratory evaluation, and storage of biological specimens for genetic or molecular analysis in this trial/future use {33}

Not applicable. No biological specimens will be collected for the study.

## Statistical methods

### Statistical methods for primary and secondary outcomes {20a}

Here, the intervention effect on the two primary outcomes will be estimated by an intent-to-treat analysis. Our first primary outcome, writing performance, will be treated as a continuous variable. Our second primary outcome, cognitive effort as measured by mean changes in pupil size, will also be treated as a continuous variable. We will estimate the intervention effect on each outcome separately using ordinary least squares (OLS) regression with heteroskedasticity-robust standard errors. To control for type I error inflation due to multiple testing, we will apply a Bonferroni correction. Accordingly, the adjusted significance threshold is set at *α* = 0.05/2 = 0.025. The outcome of cognitive effort is a psychophysiological measure recorded throughout the entire writing process. Standard pre-processing steps will be taken before the statistical analysis [51, 52], such as correcting for screen angle distortion, removing invalid data that do not reflect the actual pupil size (pupil size below 1.5 mm or over 9 mm [53], often due to blinking), smoothing to remove small oscillatory and noise activity, interpolating blink related invalid data, downsampling, and correcting pupil size changes based on the baseline pupil size that will be collected during a 30-s relaxation task at the beginning of the experiment. Participant-level data will be excluded if the data do not meet basic quality standards, such as having a high proportion of invalid data.

For the secondary outcomes, all survey scale measures will be treated similarly to the writing performance outcome. They will be viewed as continuous variables and analyzed using OLS regression with heteroskedasticity-robust standard errors. Cognitive effort, as measured by changes in the cortical hemodynamics, will be treated similarly to pupil size changes. Through a series of pre-processing steps, we will compute channel-wise hemodynamic changes in HbO using the Satori software. The raw data of two wavelengths (760 nm and 850 nm) will be trimmed so that only the fNIRS data collected during the writing task is analyzed, and bad channels will be rejected using a coefficient of variation (CV) [54]. Then, the data will be further pre-processed using a standard pipeline, including data conversion using modified Beer-Lambert law (MBLL) [55], spike removal using a robust spike detection method, motion correction using the Temporal Derivative Distribution Repair (TDDR) [56], physiological noise removal using the highest correlated channel data from the eight short channel data, temporal filtering, and normalization through the z-normalization step. After pre-processing, we will use a generalized linear mixed model to estimate the intervention effect to account for participant-level random effects.

For the above statistical modeling, we will first run the analyses without adjusting for covariates because randomization, on average, eliminates confounding. Subsequently, we will run the analyses with adjusted covariates, including participants’ self-reported skill levels and motivation, because power can often be improved with covariate adjustments, and such adjustments can improve residual confounding. For skill levels, we will include three variables based on the three aspects of self-reported skill level: writing ability, critical thinking ability, and English language ability. For motivation, we will include one variable based on participants’ self-reported motivation to achieve a high-performance score in the analytical writing task. The four variables will be viewed as continuous variables and all added to the model. Should there be variations in other baseline measures, such as gender and race, between the intervention group and the control group, we will further adjust our model to control for these potential confounding sources.

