### Outcomes {12}

The study has two primary outcomes. First, we will measure participants’ writing performance scores on the analytical writing task. The task is adapted from the Analytical Writing section in the GRE, a worldwide standardized computer-based exam developed by the Educational Testing Service (ETS) [27]. Participants’ writing performance will be scored using the GRE 0–6 rubric and by an automatic essay-scoring platform called *ScoreItNow!*, which is powered by ETS’s e-rater engine [32, 33]. We chose to adapt from the GRE writing materials for two reasons. First, their writing task and grading rubrics were established writing materials designed to measure critical thinking and analytical writing skills and have been used in research as practice materials for writing (e.g. [34]). Second, OpenAI’s technical report shows that ChatGPT (GPT-4) can score 4 out of 6 (~ 54th percentile) on the GRE analytical writing task [31]. This gives us a benchmark for assessing the potential increase in writing performance when individuals collaborate with generative AI.

Second, we will measure participants’ cognitive effort during the writing process. Participants’ cognitive effort will be measured using a psychophysiological proxy—i.e., changes in pupil size [35, 36]. Pupil diameter and gaze data will be collected using the Tobii Pro Fusion eye tracker at a sampling rate of 120 Hz. During the preparation stage of the study, the room light will be adjusted so that the illuminance at the participants’ eyes is at a constant value of 320 LUX. Baseline pupil diameters will be recorded during a resting task in the experiment preparation stage that asks the participant to stare at a cross that will appear for 10 s each on the left, center, and right sections of the computer screen. Pupil diameters and gaze data will be recorded throughout the writing process.

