### Sample size {14}

To estimate the required sample size, we conducted a simulation analysis on the intervention effect on writing performance using ordinary least squares (OLS) regression. Recent empirical evidence suggests that the effect size of generative AI on writing tasks ranges around Cohen’s *d* = 0.4–0.5, such as [1, 48]. In our simulation analysis, the simulated data assumes normally distributed data, equal and standardized standard deviations between the two conditions, and an anticipated effect size of Cohen’s *d* = 0.45. In the end, our analysis indicated that recruiting a minimum of 160 participants would be necessary to achieve a statistical power greater than 0.8 under an alpha level of 0.05. The simulation was implemented in R, and the corresponding code is available at the Open Science Framework (OSF) via https://osf.io/9jgme/.

We opt to base our sample size estimation on writing performance, but not on the other primary outcome, cognitive effort, for two reasons. First, the effect of generative AI on performance outcomes has been studied [1, 48], but we did not find prior evidence on the effect size of generative AI on cognitive effort using physiological measures. Second, our physiological measure of cognitive effort may likely be powered once the sample size satisfies our behavioral measure of writing performance. Pupillometry studies on cognitive efforts, such as the N-back test, typically recruit 20–50 participants in short, repeated, within-subject trials (e.g., [49]). These studies provide a general estimation of participants needed. Although our study design (i.e., a between-subject RCT) differs from common pupillometry studies, cognitive effort is still a repeated outcome measure using time series pupil data throughout the entire writing process. Repeated outcome measures generally can enhance statistical power by taking into account within-subject variability [50].

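### Power above 0.8 for writing performance is stated at alpha 0.05, but each primary outcome is tested at 0.025, where power is about 0.72; Holm would recover part of the loss

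*Protocol article*

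**What the plan says.** Outcomes {12} declares: "The study has two primary outcomes". They are writing performance and cognitive effort measured by pupil size.

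Statistical methods {20a} analyses each outcome in its own regression and adds, as protection against a raised type I error: "we will apply a Bonferroni correction". It then fixes the level for each test: "the adjusted significance threshold is set at *α* = 0.05/2 = 0.025".

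Sample size {14} rests on writing performance alone, with "an anticipated effect size of Cohen’s *d* = 0.45" and equal standardised standard deviations. It concludes that at least 160 participants are needed "to achieve a statistical power greater than 0.8 under an alpha level of 0.05". It reports that no earlier effect size was found for a physiological measure of cognitive effort, and so gives none for the pupil outcome.

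**The concern.** The two sections use different significance levels for the same comparison. The power claim is made at 0.05, while the test of writing performance is run at 0.025. A reader of Sample size {14} will take the trial to have better than an 80% chance of detecting d = 0.45 on writing. Under the rule in {20a} that chance is lower, so a non-significant writing result would be weaker evidence of no effect than the protocol suggests.

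A second, milder point follows. Once the stricter level has reduced power, the choice of multiplicity procedure matters more. Single-step Bonferroni holds the second test at 0.025 even after the first has succeeded. Holm's step-down rule releases it to 0.05 with the same guarantee on family-wise error.

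**Working it through.** **Inputs.** From Sample size {14} and Trial design {8}: 160 participants allocated 1:1, hence 80 per arm; d = 0.45 with standard deviation 1, from a cited range of 0.4 to 0.5; alpha 0.05. From {20a}: 0.025 per outcome. Assumed, because not stated: two-sided tests, pupil effects from d = 0 to 0.6, and correlation between the two test statistics from −0.3 to 0.3.

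**1. The plan's own figure.** Normal approximation: n per arm = 2(1.960 + 0.842)²/0.45² = 77.5, rounded up to 78 (156 in total). The t-test version gives 79 per arm (158). The standardised mean difference is 0.45 × √(80/2) = 2.846. Power at 80 per arm is Φ(2.846 − 1.960) = 0.812, or 0.808 from the noncentral t. The 160 is reproduced. A one-sided 0.05 would need only 62 per arm and does not reproduce it, which supports the two-sided reading.

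**2. The same design at 0.025.** Φ(2.846 − 2.241) = 0.727; noncentral t: 0.720. On the t basis, at 80 per arm:

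| d for writing | alpha 0.05 | alpha 0.025 |
|---|---|---|
| 0.40 | 0.710 | 0.606 |
| 0.45 | 0.808 | 0.720 |
| 0.50 | 0.882 | 0.815 |

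For 80% power at 0.025 and d = 0.45, n per arm = 2(2.241 + 0.842)²/0.45² = 93.9, so 94 (188 in total); the t version gives 96 (192).

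**3. Family-wise error under Bonferroni.** With independent statistics and no true effect, 1 − 0.975² = 0.0494. The correction works as intended.

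**4. What Holm adds.** Holm rejects for writing if its p-value is at most 0.025, or if it is at most 0.05 and the pupil p-value is at most 0.025. With independent statistics:

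Holm power for writing = 0.7197 + (0.8075 − 0.7197) × (pupil power at 0.025)

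| Assumed pupil d | Pupil power at 0.025 | Writing, Bonferroni | Writing, Holm |
|---|---|---|---|
| 0 | 0.025 | 0.720 | 0.722 |
| 0.2 | 0.162 | 0.720 | 0.734 |
| 0.3 | 0.360 | 0.720 | 0.751 |
| 0.45 | 0.720 | 0.720 | 0.783 |
| 0.6 | 0.936 | 0.720 | 0.802 |

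A simulation of one million draws per scenario agrees to within 0.001. Correlations of 0.3 and −0.3 give 0.777 and 0.790 at pupil d = 0.45. To reach 0.80 with independent statistics, pupil power at 0.025 must be (0.80 − 0.7197)/0.0878 = 0.915.

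**5. Both outcomes, and at least one,** with d = 0.45 on each and independent statistics:

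- Both, Bonferroni: 0.7197² = 0.518.
- Both, Holm: 0.8075² − 0.0878² = 0.644. The subtracted term is the case where both p-values lie between 0.025 and 0.05, so neither is rejected.
- At least one, either procedure: 1 − (1 − 0.7197)² = 0.921.

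**6. Error under Holm.** With no effect on either outcome, the chance of any false rejection is the same as under Bonferroni (0.0496 in simulation). If writing has d = 0.45 and pupil size has no effect, the pupil outcome is falsely rejected with probability 0.025 + 0.7197 × 0.025 = 0.043. This is higher than 0.025 but within 0.05, the bound that Holm guarantees under any dependence.

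**The case against.** The best defence is that {20a} contains no error. Bonferroni is prespecified, the threshold is computed correctly, and error is controlled under any dependence. Nothing in the protocol promises a stepwise rule. This stands.

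A reader might infer that Bonferroni is a mistake, or that it gives power away for nothing. The document does not support either. The single-step rule judges each outcome without regard to the other and has directly matching 97.5% intervals, which Holm lacks. Holm also adds nothing to the chance of at least one significant result.

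A reader might equally infer that Holm repairs the shortfall. It does so only when the pupil effect is large, at about d = 0.6. If there is no pupil effect, the gain for writing is about 0.2 percentage points. The tables also assume all 80 per arm contribute pupil data, whereas {20a} allows exclusion for poor-quality recordings; any such loss would shrink the gain.

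The exploratory framework in Trial design {8} lowers the stakes. It does not remove the mismatch, because the protocol itself sets a formal threshold and a formal power target.

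**Conclusion.** The power claim in Sample size {14} does not hold under the test in {20a}. For writing performance at d = 0.45 with 80 per arm, power is about 0.72 and not above 0.8. Within the cited effect range it runs from 0.61 to 0.81. This rests on two-sided tests and on all 160 participants being analysed for writing.

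Holm is an optional improvement on a valid procedure. Over the assumed pupil effects, with independent statistics, it adds between 0.2 and 8 percentage points for writing, and about 13 points for showing both effects when each is d = 0.45. How much of the loss it recovers depends on a pupil effect for which the protocol has no estimate.

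**What to change.** 1. In Sample size {14}, restate power for writing performance at 0.025: about 0.72 at d = 0.45, with 0.61 and 0.81 at d = 0.40 and 0.50. If 80% power at 0.025 is still the aim, give the matching sample size, 188 to 192 in total. Restating costs a sentence or two; enlarging the trial would cost 28 to 32 more participants.

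2. In {20a}, replace the fixed threshold with Holm: order the two primary p-values, test the smaller at 0.025 and, only if it is significant, test the larger at 0.05. Otherwise, keep Bonferroni and say why the single-step rule is preferred. Any Holm power quoted should be labelled as conditional on an assumed pupil effect. The change is one sentence and should be made before the masked analyst sees the allocation.

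3. Report 97.5% confidence intervals for both outcomes alongside the Holm decisions. Note that an outcome rejected in the second step with a p-value between 0.025 and 0.05 will have a 97.5% interval that includes zero. That awkwardness in reporting is the main cost of the switch.

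### Baseline pupil diameter is collected before the intervention but is a covariate in neither model for the co-primary pupil outcome; prespecifying it could gain precision for one degree of freedom

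*Protocol article*

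**What the plan says.** All but one of these statements are in the protocol article's section on statistical methods for primary and secondary outcomes {20a}.

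- **Outcome.** The second primary outcome is described as "cognitive effort as measured by mean changes in pupil size, will also be treated as a continuous variable".
- **Use of the baseline.** Pre-processing ends with "correcting pupil size changes based on the baseline pupil size", the baseline being a 30-s resting recording. Whether the correction is a difference or a proportion is not stated.
- **Timing.** Outcomes {12} says: "Baseline pupil diameters will be recorded during a resting task in the experiment preparation stage". The value therefore predates the writing task and any use of ChatGPT.
- **Model.** "We will estimate the intervention effect on each outcome separately using ordinary least squares (OLS) regression with heteroskedasticity-robust standard errors".
- **First analysis.** "we will first run the analyses without adjusting for covariates because randomization, on average, eliminates confounding".
- **Second analysis.** Self-reported writing ability, critical thinking ability, English ability and motivation are added: "The four variables will be viewed as continuous variables and all added to the model". One stated reason is "because power can often be improved with covariate adjustments". Other baseline measures enter only if the arms are seen to differ on them. Gender and race are the examples given; pupil size is not named.

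**The concern.** Baseline pupil diameter is the outcome's own pre-intervention value, and the plan uses it only to correct the outcome in pre-processing. If that correction is a subtraction, it fixes the slope of task pupil size on baseline at 1. Using baseline as a covariate lets the data estimate the slope. Where the true slope differs from 1, the change score stays correlated with baseline, and that part of its variance is left in the comparison.

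The omission sits oddly with the plan's own reason for adjusting. Three of its four chosen covariates (writing, critical thinking and English ability) are collected in the post-survey (Plans for assessment and collection of outcomes {18a}), whereas baseline pupil size is measured before the intervention.

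Precision on a co-primary outcome is at stake. The sample size section {14} sizes the trial on writing performance only and argues in general terms that the pupil outcome is likely to be powered as well.

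**Working it through.** **The plan's own figure.** The only sample size stated is 160, for writing performance at d = 0.45, alpha 0.05 and power above 0.8. Taking the test as two-sided (not stated), the normal approximation gives 78 per arm (156 in total) and the t-test 79 per arm (158). With 80 per arm, power is 0.812 (normal) or 0.808 (t). The figure reproduces, but it says nothing about the pupil outcome.

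**Inputs.** N = 160 and 1:1 allocation come from the protocol. The correlation ρ between baseline and mean task pupil size, and the ratio k = SD(task)/SD(baseline), are not in the documents and are assumed over a range. The formulas assume a subtractive correction and the same ρ and SDs in both arms.

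**Formulas.** Let s be the baseline SD.

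- Variance of the change score: s²(1 + k² − 2ρk)
- Residual variance with baseline as covariate: s²k²(1 − ρ²)
- Difference between the two: s²(1 − ρk)²

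The regression slope of task on baseline is ρk. The gain is therefore zero when the slope is 1 and grows as the slope moves away from 1 in either direction. With k = 1 the variance ratio (covariate model over change score) reduces to (1 + ρ)/2. Estimating one more coefficient multiplies the variance by about 1 + 1/(160 − 4) = 1.0064, or about 0.6%.

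**Equal SDs (k = 1)**

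| ρ (assumed) | Ratio (1 + ρ)/2 | With df cost |
|---|---|---|
| 0.3 | 0.65 | 0.654 |
| 0.5 | 0.75 | 0.755 |
| 0.7 | 0.85 | 0.855 |
| 0.8 | 0.90 | 0.906 |
| 0.9 | 0.95 | 0.956 |
| 0.95 | 0.975 | 0.981 |

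In participants, 1/0.75 = 1.33, 1/0.85 = 1.18 and 1/0.90 = 1.11. The change score would need 33%, 18% and 11% more participants for the same precision at ρ = 0.5, 0.7 and 0.8. At ρ = 0.9 and 0.95 the figures are about 5% (1/0.95 = 1.053) and 2.6% (1/0.975 = 1.026).

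**Unequal SDs**

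- Task SD smaller (k = 0.8): for ρ from 0.3 to 0.95 the ratio with df cost lies between 0.505 and 0.644.
- Task SD larger (k = 1.2): over the same ρ it lies between 0.767 and 1.003. At ρ = 0.8 the slope is 0.96 and the ratio is 1.44 × 0.36 / (1 + 1.44 − 1.92) = 0.5184/0.52 = 0.997, or 1.003 with the df cost. That is no gain.

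**Simulation** (80 per arm, 4,000 runs). At k = 1 the ratio was 0.745 for ρ = 0.5, 0.846 for ρ = 0.7 and 0.971 for ρ = 0.9. With a slope of exactly 1 it was 1.007 (ρ = 0.95) and 1.010 (ρ = 0.8). Both estimators averaged close to zero when no effect was simulated.

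**Choice of outcome.** Regressing (task − baseline) rather than task on arm and baseline lowers the baseline coefficient by exactly 1 and leaves the arm coefficient unchanged. This identity needs a subtractive correction.

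**The case against.** The strongest reply is that nothing here is wrong. Baseline already enters through the correction, and under 1:1 randomisation the corrected outcome compared by OLS is unbiased. The article condenses a fuller plan, and the adjusted analysis leaves some room for further baseline covariates. Unbiasedness stands, so this is a point about efficiency only. The rest carries less weight. The article states the model and names the four covariates, so it describes a choice already made. The clause on baseline differences depends on observed imbalance, does not name pupil size, and does not serve precision.

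A reader might infer several stronger things that the documents do not support:

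- **That a gain is assured and free.** Both pupil measures come from the same eyes, device and session at constant illuminance, so a high correlation or a slope near 1 cannot be excluded. In that case the gain is small or nil, and one degree of freedom is still spent.
- **That a short, noisy baseline puts the slope below 1, so chance imbalance is over-corrected.** At 120 Hz, 30 s can yield up to 30 × 120 = 3,600 samples, and no document figure fixes the slope.
- **That the outcome is a simple difference.** The form of the correction is not stated. If it is proportional, the variance formulas above do not apply.
- **That the pupil comparison is already short of power at 0.025.** Power of about 0.72 to 0.73 at that level belongs to writing performance at d = 0.45. The protocol reports finding no effect size for the physiological outcome, so its power cannot be called short or adequate.
- **That situational interest has the same fault.** It is a post-only score on four items about the completed assignment. Initial interest is three general items. The slope-of-1 argument does not apply.

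**Conclusion.** The point holds as an efficiency improvement to a stated model. Baseline pupil diameter is pre-intervention, is already collected, and is missing from both the unadjusted and the adjusted pupil model. In a 1:1 trial the OLS estimate with baseline as covariate targets the same effect and, in large samples, is never less precise than the change score.

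Under a subtractive correction and equal SDs, the variance reduction runs from about 35% at ρ = 0.3 to about 2.5% at ρ = 0.95. It is larger if task pupil size varies less than baseline, and nil when the slope is near 1. All these sizes rest on assumed ρ and k. The analysis as planned is not biased, and no loss of power on the pupil outcome can be demonstrated from the documents.

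**What to change.** Add one sentence to the statistical methods {20a}: baseline pupil diameter from the resting task is a prespecified covariate in the primary pupil model, whether or not the arms differ on it. If the correction is subtractive, either mean task pupil size or the change may be the outcome, since the arm estimate is the same; stating the form of the correction there would make this explicit. No new data are needed. The cost is one degree of freedom, about 0.6% of variance.

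As a separate and minor point, initial interest from the pre-survey can be added as a covariate when situational interest is analysed. No gain is quantified for this.

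### Baseline pupil diameter is recorded before the task but is not a prespecified covariate for the primary pupil outcome, so the planned change analysis may give up precision and robustness to chance imbalance

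*Protocol article*

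**What the plan says.** **Baseline.** Under Outcomes {12}, "Baseline pupil diameters will be recorded during a resting task in the experiment preparation stage". The participant is asked to "stare at a cross that will appear for 10 s each on the left, center, and right sections of the computer screen", which makes 3 × 10 s = 30 s, before the writing task starts.

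**Outcome.** Under Statistical methods {20a}, the second primary outcome is "cognitive effort as measured by mean changes in pupil size, will also be treated as a continuous variable". Pre-processing includes "correcting pupil size changes based on the baseline pupil size that will be collected during a 30-s relaxation task". Whether the correction subtracts or divides is not stated.

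**Model.** The same section says "We will estimate the intervention effect on each outcome separately using ordinary least squares (OLS) regression with heteroskedasticity-robust standard errors", with each primary outcome tested at 0.025.

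**Covariates.** Still under {20a}, "we will first run the analyses without adjusting for covariates because randomization, on average, eliminates confounding". After that, "we will run the analyses with adjusted covariates, including participants’ self-reported skill levels and motivation". The adjusted set is writing ability, critical thinking ability, English ability and motivation: "The four variables will be viewed as continuous variables and all added to the model". A last clause promises further adjustment if the arms turn out to differ on other baseline characteristics, with gender and race as examples. Baseline pupil diameter is not mentioned there.

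**The concern.** The protocol supports covariate adjustment on grounds of power, yet the set it lists leaves out the one pre-task measurement of the outcome itself. The baseline is used only to form a change. A subtractive change analysed on arm alone assumes that task pupil size rises one-for-one with baseline pupil size. Where it does not, the baseline still explains part of the change, and that part stays in the residual variance.

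Two things are at stake. The first is precision. Sample size {14} gives the pupil outcome no calculation of its own and expects it to be adequately powered partly because pupil size is measured repeatedly. The named analysis, however, reduces the series to a mean change in an OLS model, so precision rests on between-participant variance, which baseline adjustment can reduce. The second is robustness: for a given realised difference in baseline pupil size between arms, the change estimate is shifted by an amount the adjusted model would largely remove.

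**Working it through.** **The plan's own figure.** The only stated size is 160, for writing performance (d = 0.45, power above 0.8, alpha 0.05). With the normal approximation, 2 × (1.960 + 0.842)² / 0.45² = 77.5, so 78 per arm or 156 in total; the t-test version gives 157. The figure of 160 reproduces (power about 0.81 at 80 per arm). There is no pupil figure to reproduce.

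**Inputs.** 80 per arm (160, allocated 1:1) and alpha 0.025, taken as two-sided. Not in the protocol, and therefore assumed: the baseline-to-task correlation ρ, the ratio k = task SD / baseline SD, and subtractive correction.

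**Formulas, in units of baseline variance.**
- Slope of task on baseline: ρk.
- Residual variance with baseline in the model: A = k²(1 − ρ²).
- Variance of the change: C = k² + 1 − 2ρk = A + (ρk − 1)².

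Since C exceeds A by (ρk − 1)², the change analysis is asymptotically never more precise. The two are equal only when the slope is 1. With k = 1 the ratio A/C reduces to (1 + ρ)/2.

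- Shift of the change estimate for a baseline difference D between arms: (ρk − 1) × D.
- One standard error of D is √(2/80) = 0.158 baseline SD. An imbalance of that size shifts the change estimate by (ρk − 1)/√C of its own standard error.

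| k | ρ | slope | A | C | A/C | shift at 1-SE imbalance (in SE of the change estimate) |
|---|---|---|---|---|---|---|
| 1.0 | 0.5 | 0.50 | 0.750 | 1.000 | 0.75 | −0.50 |
| 1.0 | 0.7 | 0.70 | 0.510 | 0.600 | 0.85 | −0.39 |
| 1.0 | 0.9 | 0.90 | 0.190 | 0.200 | 0.95 | −0.22 |
| 0.8 | 0.5 | 0.40 | 0.480 | 0.840 | 0.57 | −0.65 |
| 0.8 | 0.7 | 0.56 | 0.326 | 0.520 | 0.63 | −0.61 |
| 0.8 | 0.8 | 0.64 | 0.230 | 0.360 | 0.64 | −0.60 |
| 0.8 | 0.9 | 0.72 | 0.122 | 0.200 | 0.61 | −0.63 |
| 1.2 | 0.5 | 0.60 | 1.080 | 1.240 | 0.87 | −0.36 |
| 1.2 | 0.7 | 0.84 | 0.734 | 0.760 | 0.97 | −0.18 |
| 1.2 | 0.8 | 0.96 | 0.518 | 0.520 | 1.00 | −0.06 |
| 1.2 | 0.9 | 1.08 | 0.274 | 0.280 | 0.98 | +0.15 |

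**In participants, equal SDs.** To match the adjusted analysis of 160, a change analysis would need 160/0.75 = 213, 160/0.85 = 188 or 160/0.95 = 168 participants at ρ 0.5, 0.7 or 0.9.

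**In power, equal SDs.** Suppose the change test had 80% power at two-sided 0.025. The adjusted test would then have about 90.6%, 86.5% or 82.2% at the same three correlations. This needs no assumed pupil effect size.

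**Simulation check** (3,000 runs for each ρ, 80 per arm, k = 1, OLS with HC3 standard errors). At ρ = 0.5, 0.8 and 0.9 the variance ratios were 0.749, 0.899 and 0.953, against 0.75, 0.90 and 0.95 in theory. Per unit of baseline imbalance the change estimate moved by −0.52, −0.21 and −0.11, and the adjusted estimate by about −0.02 to −0.01. Averaged over all runs, the error of either estimate was at most 0.004 in size, so neither is biased over repeated randomization.

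**The case against.** Baseline-corrected pupil change is a legitimate outcome, and the protocol openly chooses an unadjusted analysis followed by an adjusted one, in a study it calls exploratory. Four stronger readings are tempting, and the document supports none of them.

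- **That the planned estimate is biased or its test invalid.** It is neither. The shift is conditional on the imbalance that happens to occur and averages out over randomization. With equal SDs and ρ = 0.7, an imbalance of 0.2 SD (0.2/0.158 = 1.3 standard errors) shifts the estimate by 0.3 × 0.2 = 0.06 SD. That is 0.06/√0.6 = 0.08 SD of the change, about half its standard error.
- **That the slope must be below 1.** A short resting baseline makes this plausible, but no correlation or SD is given. With a task SD 1.2 times the baseline SD and ρ from 0.7 to 0.9, the slope runs from 0.84 to 1.08 and the gain almost disappears.
- **That baseline pupil size can enter no model.** The clause on other baseline measures that differ between arms could admit it. That route depends on the observed data, does not name the variable and leaves the first analysis as it is. It weakens the point without answering it.
- **That the gain can be stated as power at d = 0.45.** That effect size belongs to writing performance. Sample size {14} says no prior effect size was found for the physiological measure.

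It also stands that the form of correction is open and may be settled in a fuller analysis plan. If it is divisive, these figures do not apply as they are, though baseline would still be a sensible covariate. The covariate list itself is not left open: the article names four variables, and this one is not among them.

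**Conclusion.** The point holds as one of efficiency and robustness. Neither the first analysis nor the listed adjusted set includes baseline pupil diameter, although it is already recorded before the task. Assuming subtractive correction, adding it cannot lose precision asymptotically and removes most of the sensitivity to chance baseline imbalance.

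The size of the gain cannot be fixed from the protocol. Over the range examined, the variance saving runs from essentially nothing (slope near 1) to 43% (SD ratio 0.8, ρ = 0.5). With equal SDs it is 25%, 15% and 5% at ρ 0.5, 0.7 and 0.9. The reason to act is that the remedy costs almost nothing and the pupil outcome has no sample-size calculation of its own to fall back on.

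**What to change.** In Statistical methods {20a}, prespecify baseline pupil diameter as a covariate in every OLS model for the pupil outcome, including the primary one, with robust standard errors as planned. The outcome may be the mean task pupil size or its subtractive change; with baseline in the model, both give the same arm effect. Keep the three skill variables and motivation as the additional set for the adjusted analysis, so that baseline pupil size does not depend on the imbalance clause. Leave the writing-score models unchanged.

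Cost: a sentence or two in the statistical section and one degree of freedom. No new data are needed.
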